## Abstract

**Background:**

Accreditation is used increasingly in health systems worldwide. However, there is a lack of evidence on the effects of accreditation, particularly in general practice. In 2016 a mandatory accreditation scheme was initiated in Denmark, and during a 3-year period all practices, as default, should undergo accreditation according to the Danish Healthcare Quality Program. The aim of this study is primarily to evaluate the effects of a mandatory accreditation scheme.

**Methods/design:**

The study is conducted as a cluster-randomized controlled trial among 1252 practices (clusters) with 2211 general practitioners in Denmark. Practices allocated to accreditation in 2016 serve as the intervention group, and practices allocated to accreditation in 2018 serve as controls. The selected outcomes should meet the following criteria: (1) a high degree of clinical relevance; (2) the possibility to assess changes due to accreditation; (3) availability of data from registers with no self-reporting data. The primary outcome is the number of prescribed drugs in patients older than 65 years. Secondary outcomes are changes in outcomes related to other perspectives of safe medication, good clinical practice and mortality. All outcomes relate to quality indicators included in the Danish Healthcare Quality Program, which is based on general principles for accreditation.

**Discussion:**

The consequences of accreditation and standard-setting processes are generally under-researched, particularly in general practice. This is the largest study in general practice with a randomized implementation approach to evaluate the clinical effects of a nation-wide mandatory accreditation scheme in general practice.

**Trial registration:**

ClinicalTrials.gov, NCT02762240. Registered on 24 May 2016.

**Electronic supplementary material:**

The online version of this article (doi:10.1186/s13063-017-1818-6) contains supplementary material, which is available to authorized users.

## Background

Accreditation is a procedure in which a recognized external institution evaluates an organization on the basis of a predefined set of quality standards. This usually involves a formal site visit by a team of surveyors [1]. The evaluation results in a decision on the granting of accreditation status. Accreditation has become a widespread tool for quality control and improvement in healthcare, and many resources are spent on developing and implementing accreditation systems across the world [2]. Nevertheless, solid evidence for the effects of accreditation is generally lacking, and this is particularly true for general practice [3, 4]. Only two effect studies on accreditation met the quality standards for inclusion in the first Cochrane review [5] on the subject, and none of these studies were about accreditation in general practice. Further, a review on the status of accreditation in primary care concluded that there is a dearth of research on the nature and uptake of accreditation in this sector along with how accreditation affects outcomes of care, and whether it is an effective method to improve quality, perceptions of care, healthcare utilization and costs [3]. In addition to a call for evidence of the clinical effects of accreditation, healthcare professionals have expressed concerns about the bureaucracy and the extra registration work imposed by accreditation.

In 2014 it was decided to implement a mandatory accreditation scheme in Danish general practice in the period 2016–2018. This protocol paper describes the design of a cluster-randomized evaluation of this accreditation scheme by means of the Consolidated Standards of Reporting Trials (CONSORT) extension and the Standard Protocol Items: Recommendations for Interventional Trials (SPIRIT) statement for cluster-randomized trials (Additional files 1 and 2).

## Methods/design

### Participants and study design

The accreditation scheme in Denmark is rolled out as a cluster-randomized controlled trial (CRCT). All 1922 general practices are eligible for the study and are allocated to undergo accreditation in 2016, 2017 and 2018 respectively. Practices allocated to accreditation in 2016 (accreditation2016) and representing 604 clusters are selected as the intervention group, while practices allocated to accreditation in 2018 (accreditation2018) represent 648 clusters and serve as the control group. Practices are assigned an accreditation date 1 year in advance, and in order to avoid contamination from the intervention group, practices allocated to accreditation in 2017 (accreditation2017), representing 664 practices, will be excluded from analysis.

This design, in addition to the comprehensive Danish National Health registers, offers a unique opportunity to conduct research on the effects of accreditation [6–8]. Moreover, the design makes possible a comparison of practices that have already accomplished accreditation with practices waiting to be accredited [9]. Additionally, the national Civil Registration System (CRS) facilitates the collection of relevant data independent of the involved practices [10].

The Danish healthcare system is tax-financed, and most general practitioners (GPs) and hospital services are free of charge. General practice is characterized by five key components. (1) There is a list system associating citizens with a GP. GPs can close for uptake when they have 1600 persons on the list but are allowed to enroll up to 2550 persons. (2) The GP acts as gatekeeper and first-line provider in the sense that a referral from a GP is required for most office-based specialists and always for inpatient and outpatient hospital treatment. (3) An after-hours system is staffed by GPs on a rotation basis. (4) There is a mixed capitation and fee-for-service system. (5) GPs are self-employed, working on contract for the public funder based on a national agreement that details not only services and reimbursement but also opening hours and required postgraduate education [11]. Danish general practice constitutes 1922 practices comprising a total of 3329 GPs.

The accreditation program is developed and managed by the Danish Institute for Quality and Accreditation in Healthcare (IKAS). IKAS offers a range of accreditation programs, tailored for private hospitals, community pharmacies, community healthcare, general practice and specialist physicians practicing outside of a hospital setting.

One year in advance, practices are notified about their accreditation date by letter from IKAS. It is expected that practices will begin working with the standards from that date onwards.

### Randomization

IKAS decided that surveys in all five regions of Denmark should be evenly distributed for the 3 years during which the accreditation process takes place. Moreover, it was decided by IKAS that the accreditation should be conducted by means of municipalities (each Danish region is divided into several smaller municipalities) and that the order of municipalities should be completely random.

Time for accreditation of the practices in the 98 municipalities in Denmark was determined in a randomized lots drawing conducted on 22 September 2014 by IKAS, and provided the basis for a prospective study. Two impartial persons from IKAS conducted the drawing. Within each of the five Danish regions, one-third of the practices within the municipalities that were drawn first were allocated to accreditation in 2016, the next third to 2017 and the last third to 2018. If large municipalities were drawn and this resulted in an excess of practices greater than one-third of the practices in a region, the practices were split over 2 allocation years based on the first letter in the street name in ascending order (Fig. 1).

**Fig. 1 Fig1:**
[figure not shown]
Trial flow for accreditation in general practice (AKIAP)

This randomization allows for comparisons between early accredited practices (2016, *n* = 604 practices) and late accredited practices (2018, *n* = 648 practices) in 2017. Every practice is considered a cluster, which means that there are 1252 clusters in the study. The CRCT study is designed to comply with the recommendations of the CONSORT statement: extension to cluster-randomized trials [12] and SPIRIT.

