### Statistics

Differences in baseline characteristics are reported as numbers (percentages) and tested using chi-squared tests.

Linear regression will be used for continuously valued outcomes (e.g. number of different drugs, safe medication, annual controls, etc.) and logistic regression for binary outcomes (polypharmacy, preventive home visits, changes in proportion of practices with reported adverse events and changes in proportion of practices with a patient satisfaction survey). Analyses will account for clustering of patients in practices by generalized estimating equations (GEE). A level of 5% will be taken as statistically significant.

Analyses will be performed in SAS version 9.4 (SAS Institute, Cary, NC, USA).

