### Power calculation

The mean number of Danes older than 65 years allocated to an average practice is 584 (standard deviation (SD) 378; registry data at the start of 2015). The mean number of redeemed prescriptions per patient among Danes older than 65 years is 6.59 (SD 5.04; registry data over the full year 2014). For the power calculation, the intra-class correlation (ICC) is set relatively high at 0.2.

Using the formulae in Hemming et al. [19], we are able with our data to detect a difference from a mean number of prescriptions of 6.59 in the control group to 6.13 in the accreditation group using a *t* test with a 5% level of significance accounting for clustering within practices with a power of 80%.

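### Lots were drawn for municipalities, but the analysis and power calculation treat the 1252 practices as the independent clusters; the 5% test is anti-conservative if practices in the same municipality are positively correlated

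*Protocol article*

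**What the plan says.** Under Randomization, the article says that "Time for accreditation of the practices in the 98 municipalities in Denmark was determined in a randomized lots drawing" and that "the order of municipalities should be completely random". The allocation rule was sequential: "Within each of the five Danish regions, one-third of the practices within the municipalities that were drawn first were allocated to accreditation in 2016", with the following thirds going to 2017 and 2018. The one departure from whole-municipality allocation concerns large municipalities that overfilled a third. In that case "the practices were split over 2 allocation years based on the first letter in the street name in ascending order". That is a fixed rule, not a draw of practices.

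The text with Fig. 1 sets out the comparison as "early accredited practices (2016, *n* = 604 practices) and late accredited practices (2018, *n* = 648 practices) in 2017" and then declares: "Every practice is considered a cluster, which means that there are 1252 clusters in the study". Participants and study design likewise counts 604 and 648 clusters. Statistics says "Analyses will account for clustering of patients in practices by generalized estimating equations (GEE"), and Power calculation describes a t test "accounting for clustering within practices with a power of 80"%. Neither section mentions municipality, and neither mentions region as a stratum.

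**The concern.** The unit that was randomised and the unit treated as independent are different. GEE with practice as the cluster protects against correlation between patients of one practice, but it assumes that two practices in one municipality are independent. Practices in a municipality nearly always share an arm, because they share a lot. Anything that moves them together between 2014 and 2017 therefore adds variance to the arm contrast that the planned standard error does not see.

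The gap is plainest for the two outcomes with one value per practice: any adverse event reported, and a patient satisfaction survey conducted. They have no patients to cluster, so the planned GEE gives them no protection against correlation between practices.

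At stake are the level of the 5% test and the width of the confidence intervals. The primary outcome is affected, and so is each secondary outcome for which practices in a municipality are positively correlated. The detectable difference is also derived with practices as the top level.

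**Working it through.** **Inputs from the article.** Practices per arm 604 and 648; mean 584 patients over 65 per practice, SD 378 (CV 378/584 = 0.647); outcome SD 5.04; ICC within practice 0.2; difference 6.59 − 6.13 = 0.46; 5% level, 80% power; 98 municipalities; 1922 practices.

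**Assumptions.** Two-sided test and normal approximation. J = 1922/98 = 19.6 practices per municipality. Municipalities in the two compared years: 98 × 2/3 ≈ 65. ρ is the correlation between practice means in the same municipality. The CV of practices per municipality, cvJ, runs from 0 to 1. The documents give neither ρ nor cvJ.

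**Step 1: the plan's own figure.** SE = 5.04 × √[DE/584 × (1/604 + 1/648)], and the detectable difference is (1.960 + 0.842) × SE.

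- Equal practice sizes: DE = 1 + 583 × 0.2 = 117.6; SE 0.128; detectable difference 0.358; power at 0.46 is 94.9%.
- Varying practice sizes: DE = 1 + [(1 + 0.647²) × 584 − 1] × 0.2 = 166.5; SE 0.152; detectable difference 0.426; power at 0.46 is 85.6%.

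The stated 0.46 is not reproduced exactly, but it errs on the cautious side at practice level.

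**Step 2: add the municipality.** The variance of the arm contrast is multiplied by DE2 = 1 + [(1 + cvJ²) × J − 1] × ρ. The true size of the nominal 5% test is 2 × [1 − Φ(1.96/√DE2)]. In the table, the first figure is for cvJ = 0 and the second for cvJ = 1. The last two columns use varying practice sizes.

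| ρ | SE ratio √DE2 | True size | Detectable difference | Power at 0.46 |
|---|---|---|---|---|
| 0 | 1.00 | 5% | 0.426 | 85.6% |
| 0.005 | 1.05–1.09 | 6.1–7.3% | 0.446–0.465 | 82–79% |
| 0.01 | 1.09–1.18 | 7.2–9.6% | 0.464–0.501 | 79–73% |
| 0.025 | 1.21–1.40 | 10.5–16.1% | 0.516–0.596 | 70–58% |
| 0.05 | 1.39–1.71 | 15.8–25.1% | 0.593–0.728 | 59–43% |

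For example, at ρ = 0.01 and cvJ = 0, DE2 = 1 + 18.6 × 0.01 = 1.186, √DE2 = 1.089, and the true size is 7.2%.

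**Step 3: how much correlation the power slack absorbs.** Power at 0.46 stays at 80% while DE2 ≤ [0.46/(2.802 × SE)]².

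- Varying practice sizes: the limit is 1.164, so ρ ≤ 0.164/18.6 ≈ 0.009.
- Equal practice sizes: the limit is 1.648, so ρ ≤ 0.648/18.6 ≈ 0.035.

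Both limits take equal-sized municipalities; unequal ones lower them.

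**Step 4: is there an offset within municipalities?** A split spans two allocation years. If these are consecutive, as sequential filling implies, no municipality has practices in both the 2016 and the 2018 arm. No within-municipality comparison then reduces the inflation.

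**The case against.** Four points can fairly be made for the plan.

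- **Outcomes are changes.** The primary outcome, and the secondary outcomes too, are changes between a 2014 baseline and a 2017 follow-up. Stable features of a municipality, such as age mix or deprivation, largely cancel. What counts is correlation in the change, which may be small. This stands, and it is why the low end of the range must be shown. It lowers the correlation but gives no ground for taking it as zero.
- **Region strata.** The draw was made within regions, and an analysis that ignores a balanced stratum tends to overstate the standard error. This stands as a partial offset.
- **Slack in the power calculation.** The ICC of 0.2 is described as set high, and 0.46 is larger than the article's inputs require. This stands for power. It does nothing for the level of the test, because the assumed ICC does not enter the analysis.
- **Practice is the unit that undergoes accreditation, and Table 1 shows balance.** This does not help. Inference has to follow the unit that was allocated, and balance on GP characteristics is not independence between practices.

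An unseen analysis plan does not remove the point either. The article does not leave the cluster open; it states which unit it is.

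A reader might infer that the standard errors are certainly too small for every outcome, or that the type I error is some specific high figure. The documents support neither, because they report no correlation between practices of a municipality, either in level or in change.

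**Conclusion.** The mismatch is established by the article's own text. Allocation was by municipality, roughly 65 units in the two compared years, while the declared clusters, the GEE and the power calculation stop at the practice. The direction follows for any outcome on which practices in a municipality are positively correlated: the standard error is too small and the test anti-conservative.

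The size is conditional. Over assumed correlations of 0.005 to 0.05 and municipality-size CV of 0 to 1, the true level runs from about 6% to 25%. These figures make no allowance for the region offset. They rest on the normal approximation and on 19.6 practices per municipality.

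A reader might also conclude that the trial is underpowered. That is not shown. The 0.46 falls short of 80% power only if the correlation exceeds about 0.009 with varying practice sizes, or 0.035 with equal sizes, taking equal-sized municipalities.

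The correction should be made before analysis. It bears on the primary outcome, and the article says outcome data could not be retrieved until autumn 2017, so it could be prespecified.

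**What to change.** - In the text with Fig. 1, replace the statement that each practice is a cluster with one naming the municipality as the unit of randomisation, drawn within region, with practices nested in it. Describe the street-name splits as the exception. Report the number of municipalities per arm and how many were split.
- In Statistics, specify GEE or a mixed model with municipality as the top-level cluster, practices nested, small-sample corrected standard errors with t degrees of freedom, and region as a fixed effect. Alternatively, specify a randomisation test that re-runs the within-region draw, including the split rule. Apply the same approach to the two practice-level outcomes.
- In Power calculation, restate the detectable difference with a municipality-level correlation, either over a range or estimated from register data. The sample is the fixed national rollout, so this informs interpretation and cannot change the size.

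The work is small: the municipality of each practice is known from the draw, and no new data are needed. The price is wider confidence intervals and a less favourable detectable difference.

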### Intervention

Since 2009 accreditation under the Danish Healthcare Quality Program (DHQP) has been mandatory in the secondary healthcare system in Denmark, and it was decided as part of ’the national strategy for quality development in the healthcare system – common aims and plan of action 2002–2006’. The DHQP has been adjusted to include general practice. The intervention comprises the rollout of a mandatory accreditation scheme, which is defined and carried out by an acknowledged, impartial institution: IKAS.

The DHQP is based on general principles for accreditation. The model contains a set of accreditation standards as well as an accreditation process [13]. The accreditation standards were developed by IKAS in collaboration with representatives from the Organization of General Practitioners in Denmark (PLO), Danish Regions, Danish Patients, and the Danish Association of Practicing Medical Specialists. A preliminary version of the standard set was pilot-tested in 26 practices in 2012 [14]. Subsequently, the standard set was further adjusted, and the Danish Regions and the PLO approved the current version in 2014.

The DHQP for general practice consists of 16 standards with associated indicators within the following areas: (1) quality and patient safety, (2) patient safety critical standards, (3) good patient continuity of care and (4) management and organization [13].

The standards include certain minimal requirements, but are also written to stimulate quality improvement. Not everything in the standards is written to describe and delineate precisely what the client should do. Parts of the standards are intended to stimulate reflection on one’s own practice and thereby inspire improvement activities.

Each standard includes a descriptive part, where the purpose and meaning of the standard is explained in more or less detail, as appropriate. Furthermore, each standard includes a number of indicators that comprise the measurable elements of the standard set. Compliance with the standard set is assessed by rating of the indicators. The surveyor team does this during survey.

A survey implies a visit from a surveyor team consisting of healthcare professionals who have received specific training to handle this task. Some surveyors in the practice sectors are IKAS employees, but all survey teams will include surveyor(s) who are peers, working most of their time in healthcare.

The survey has a dual purpose: to assess compliance with minimal requirements and to identify opportunities for improvement, even when the threshold for obtaining accreditation has been reached. A client needs to comply with the minimal requirements in order to obtain accreditation. But the survey should also give the client feedback on his or her efforts to meet the purpose of the standards, and it should do this in a way that inspires and supports quality improvement work.

Compliance assessment is governed by defined rating principles. The fundamentals are the same for all programs:Met: The client in all essentials complies with the requirements in the indicator.Largely Met: There are opportunities for improvement, but accreditation can be awarded; no further action is required.Partially Met: There are opportunities for improvement, and action is required, unless accreditation is awarded with comments or, in case of critical non-compliances, is denied.Not Met: There is no evidence for compliance or only plans to achieve compliance [13].

The standards are accompanied by rating principles, describing how compliance with the indicators is assessed and rated [13].

### Objectives

The aim of this study is to evaluate the effects of accreditation in general practice with regard to certain clinical outcomes (Fig. 2).

**Fig. 2 Fig2:**
[figure not shown]
SPIRIT flow diagram for the AKIAP project

### Clinical outcomes

The selected outcomes should meet the following criteria: (1) a high degree of clinical relevance, (2) the possibility to assess changes due to accreditation, (3) the availability of data independent of self-reporting from practices. Table 1 lists GPs and practice characteristics. The selected outcomes, their origin from the DHQP and the used data collection sources are listed in Table 2.

**Table 1 Tab1:** GP and practice characteristics distributed on randomization groups

	Accreditation in 2016	Accreditation in 2018	Total	*p* value χ^2^ test
GPs	1106	1105	2211	
Age				
Mean	53.44	52.91		*t* test: 0.64
Gender				0.32
Male	572	548	1120	
	(52%)	(50%)	(51%)	
Female	534	557	1091	
	(48%)	(50%)	(49%)	
Practice type				0.08
Single-handed	314	351	665	
	(28%)	(32%)	(30%)	
Partnership	792	754	1546	
	(72%)	(68%)	(70%)	
Region				0.71
Capital	316	330	646	
	(28%)	(30%)	(29%)	
Central Denmark	272	269	541	
	(25%)	(24%)	(25%)	
North Denmark	113	94	207	
	(10%)	(9%)	(9%)	
Zealand	155	157	312	
	(14%)	(14%)	(14%)	
Southern Denmark	250	255	505	
	(23%)	(23%)	(23%)

**Table 2 Tab2:** Description of outcomes according to DHQP standards and data sources

Primary outcome	DHQP standard ’aim’	Rationale	Data source
Changes in number of prescribed drugs in patients older than 65 years in period	2.2. Prescriptions and prescription renewal: *“Physicians in the practice have knowledge about the basic list for rational pharmacotherapy. The practice conducts, according to medical judgments, annual controls in patients with chronic disease, comprising assessment of prescriptions”.*	Inappropriate use of many concurrent drugs, especially in older people, imposes a substantial burden of adverse drug events, ill health, disability, hospitalization, and even death. National guidelines for general practice recommend critical reviews of the elderly patients’ medication, and secure medication in elderly patients relates to all four areas in DHQP, but most of all it relates to the patient security critical standards	Medication Database (MD)
Secondary outcomes			
Polypharmacy in aged patients >65 years Polypharmacy Yes/No	2.2. Prescriptions and prescription renewal: *“Physicians in the practice have knowledge about the basic list for rational pharmacotherapy. The practice conducts, according to medical judgements, annual controls in patients with chronic disease, comprising assessment of prescriptions”.*	National guidelines for general practice recommend critical reviews of the elderly patients’ medication (18)(18)(18)(15)(19)(18), and secure medication in elderly patients relates to all four areas in DHQP, but most of all it relates to the patient security critical standards. This variable is the dichotomized primary outcome defining polypharmacy as more than 5 concurrent prescribed medications.	Medication Database (MD)
Patients >65 years taking NSAIDs without a concurrent prescription for proton pump inhibitor (PPI) Daily drug dose (DDD) of NSAID without PPI in period	2.2. Prescriptions and prescription renewal: *“Physicians in the practice have knowledge about the basic list for rational pharmacotherapy. The practice conducts, according to medical judgements, annual controls in patients with chronic disease, comprising assessment of prescriptions”.*	Non-steroidal anti-inflammatory drugs (NSAIDs) can cause serious gastrointestinal complications, and it is estimated that more than 100 persons die from NSAID-induced gastrointestinal bleeding and perforation in Denmark annually. The risk is higher in the elderly. PPIs reduce the prevalence of bleeding gastric ulcers and reduce the risk of dyspepsia and uncomplicated gastric ulcers in NSAID treatment. Therefore, PPI treatment is recommended in combination with NSAIDs where these are requisite in patients older than 65 years of age.	Medication Database (MD)
Sleeping medication Indicator: reduction in DDD sleeping medication/1000 patients DDD sleeping medicine in period	2.2. Prescriptions and prescription renewal: *“Physicians in the practice have knowledge about the basic list for rational pharmacotherapy. The practice conducts, according to medical judgements, annual controls in patients with chronic disease, comprising assessment of prescriptions”.*	National guidelines from the National Board of Health recommend reduction in the prescription of sleeping medication.	Medication Database (MD)
Preventive home visits Indicator: Changes in percentage of patients >75 years who have had a preventive home visit Preventive home visit Yes/No	1.2. Use of good clinical practice – vulnerable patient groups: *“Patients are diagnosed, treated and provided support for self care and they are controlled, referred and rehabilitated in accordance with good clinical practice”*	The care of fragile elderly has a high priority and is addressed in this standard. Moreover, a specific fee for conducting preventive home visits to fragile elderly is part of the general practice remuneration system.	The Danish National Health Services Register
Annual controls for chronic disease Indicator: changes in number of conducted annual controls for chronic disease/1000 patients Number of annual controls in period	1.2. Use of good clinical practice – chronic disease: *“Patients are diagnosed, treated and provided support for self care and they are controlled, referred and rehabilitated in accordance with good clinical practice”*	Danish GPs coordinate most of chronic disease management and conduct annual controls. Remuneration for annual control is possible, only once a year, for certain chronic diseases: diabetes, psychiatric disease, cardiovascular disease (CVD), osteoporosis, chronic obstructive pulmonary disease (COPD), musculoskeletal disease, dementia and cancer.	The Danish National Health Services Register
Spirometry in COPD/asthma Indicator: changes in number of conducted spirometry/1000 patients Spirometry Yes/No in period	1.2. Use of good clinical practice – chronic disease: *“Patients are diagnosed, treated and provided support for self-care and they are controlled, referred and rehabilitated in accordance with good clinical practice”*	COPD and asthma patients should be monitored on an annual base with spirometry. GPs are remunerated with a certain fee for conducting spirometry.	The Danish National Health Services Register
Number of reported adverse events (RAEs) Indicator: changes in number of RAEs RAE Yes/No in period per practice	1.3. Reported adverse events – the aim of the standard is to: “*Reduce the risk of patient injuries following adverse events and to create learning and improvement on the background of reported adverse events”.*	Reporting of accidental events is addressed in standard 1.3. It is not only the aim to reduce the *incidence* of accidental events, but also to improve the management and learning potential of accidental events. Consequently, a simple count of RAEs may be equivocal. In order to avoid bias, we only analyse if at least one RAE has been reported from a practice in period.	Danish Patient Safety Database (DPSD)
Patient satisfaction survey Changes in proportion of practices with a patient satisfaction survey in period	1.4. Patient evaluations – the aim of the standard is to: *“Generate learning and improve the clinic’s services on the basis of patient feedback”.*	Patient-experienced quality will be surveyed using data from DANPEP (Danish Patients Evaluate Practice) (23, 24). DANPEP is a nationwide, continuous assessment of patient contentment in general practice. We only evaluate if a patient satisfaction survey is conducted in period.	DANPEP database (Danish Patients Evaluate Practice).
Mortality Indicator: changes in mortality rates (deaths/1000 inhabitants) Number of deaths in 2-month period after index date		Mortality is the ultimate measure for effects of all applied interventions in health sciences. Any changes in mortality rates in relation to accreditation are of interest and should be a focus for analysis. Data on mortality rates can be obtained from (SD).	Danish Register of Causes of Death

*SD* Statistics Denmark (StatDen)

